### CPAP treatment

CPAP treatment will be prescribed according to the following guidelines of the Spanish Society of Pneumology (SEPAR):^1^ an apnea-hypo apnea index (AHI) ≥30 h^−1^ regardless of the presence of cardiovascular comorbidity or hypersomnia or an AHI ≥ 5 h^−1^ accompanied by excessive daytime sleepiness (ESS ≥ 12) or cardiovascular comorbidity. CPAP titration will be performed using an automatic CPAP device (Autoset-T, Resmed, Sidney, Australia) according to previously described methodology.^21^

### Follow-up

All enrolled patients will undergo the same 6-month course of follow-up regardless of study arm. Patients undergoing CPAP treatment will be visited after 15 days, 1, 3, and 6 months to assess adherence to treatment (hours/day and pressure as provided by the CPAP device), solve potential issues related to CPAP utilization, and measure daytime sleepiness (ESS). CPAP pressure might be modified, when necessary, to better suit a patient’s requirements. Possible side effects of treatment as well as variables related to the care and maintenance of the CPAP equipment will be collected. Patients diagnosed with OSA who do not require CPAP treatment will be evaluated at 3 and 6 months. Finally, non-OSA patients will be visited only at 6 months. All follow-up visits will be held at the PC unit or SU according to the patient’s study arm.

### Study variables and data collection

The following variables will be collected at recruitment and at the 6-month follow-up: (i) clinical variables, including age, sex, daytime sleepiness (ESS), blood pressure, and drug use habits; (ii) anthropometric variables, including weight, height, BMI, and neck, waist and hip circumferences; (iii) comorbidities, including depression, anxiety, hypertension, heart, neurological, or respiratory diseases, non-active neoplasm, diabetes, and dyslipidemia; (iv) PSG or RP variables, including recording time, AHI, saturation <90% (CT90); and (v) quality of life (EuroQol-5D) and work or traffic accidents. Additionally, the compliance of patients undergoing CPAP treatment will be determined by dividing the number of hours of use (obtained from the internal clock of the CPAP device) by the number of days of treatment; adequate compliance will be defined as CPAP use ≥4 h/day. The final follow-up visit will also include an visual analog questionnaire on satisfaction about the received care in addition to an estimation of the overall direct costs of the treatment based on (i) sleep test costs (RP, PSG, and titration by automatic CPAP); (ii) CPAP treatment costs; (iii) patients’ travel costs; and (iv) healthcare costs 6 months before and after randomization, including number of PC and SU consultations and number and duration of emergency or day hospital admissions. Hospital and PC costs will be assessed using prices provided by the Catalan Institute of Health.^22^

### Sample size calculation

According to the literature, a calculation will be performed to support a non-inferiority analysis with ESS as the main study variable. A loss of 30% will be assumed,^23^ as well as an alpha error = 0.05, a beta error = 0.2, a non-inferiority limit of −2, and a common standard deviation for the two groups of ±5.9 for the principal variable.^24^

### Statistical analysis

Efficacy assessment will include per protocol analysis, excluding subjects who do not complete the follow-up. Adjusted analysis of covariance will be used to compare changes in ESS before and after the intervention in each study arm (non-inferiority margin = −2 points). *χ*
^2^ tests and *t*-tests (or non-parametric equivalents) will be used to compare quality of life (EuroQol-5D) and adherence to treatment in the 2 study arms as appropriate. Stratified analyses by CPAP treatment will be performed.

Cost-effectiveness assessment will include an intention-to-treat analysis to assess the total costs for each arm based on treatment effectiveness (ESS and EuroQol-5D). This will be performed using Bayesian cost-effectiveness techniques. The cost-effectiveness ratio of each treatment, the incremental cost-effectiveness ratio, the cost-effectiveness plane, the net benefit (NB) of each treatment, the incremental NB, and the cost-effectiveness acceptability curve will be considered.

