## Methods

### Design

This is an open-label, parallel, prospective, randomized controlled trial. Figure 1 shows the study flow diagram. Patients will be consecutively included while attending visits with PC physicians due to suspected OSA or resistant hypertension. The included patients will be randomized by PC personnel to either PC or SU management in a 1:1 ratio. The patients randomized to SU management will be forwarded to the SU. Finally, after achieving an appropriate diagnosis and completing a 6-month course of follow-up, outcome evaluation and cost-effectiveness analysis will be performed. This research was approved by the Ethical Committee for Clinical Research of the Hospital Arnau de Vilanova—Santa Maria (Lleida, Spain), and the trial has been registered at ClinicalTrials.gov Id: NCT02234765.

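### The only efficacy analysis named for the ESS non-inferiority test drops everyone who does not complete follow-up (84 of 280 at the planned loss), while cost-effectiveness on the same outcome is by intention-to-treat

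*Protocol article*

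**What the plan says.** All references are to the protocol article.

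- **Design:** "This is an open-label, parallel, prospective, randomized controlled trial".
- **Sample size calculation:** "a calculation will be performed to support a non-inferiority analysis with ESS as the main study variable". The margin is −2, the standard deviation 5.9, alpha 0.05 and beta 0.2. On attrition: "A loss of 30% will be assumed".
- **Statistical analysis, efficacy:** "Efficacy assessment will include per protocol analysis, excluding subjects who do not complete the follow-up". Then: "Adjusted analysis of covariance will be used to compare changes in ESS before and after the intervention in each study arm", with the −2 margin attached. Failure to complete follow-up is the only exclusion stated.
- **Statistical analysis, economics:** "Cost-effectiveness assessment will include an intention-to-treat analysis to assess the total costs for each arm based on treatment effectiveness (ESS and EuroQol-5D"). ESS is therefore an effectiveness measure here too, in an intention-to-treat population.
- **Follow-up:** the visit schedule depends on diagnosis and treatment. Patients on CPAP "will be visited after 15 days, 1, 3, and 6 months", with ESS measured. OSA patients without CPAP are evaluated at 3 and 6 months, and ESS is not mentioned for the 3-month visit. Patients without OSA are seen only at 6 months. Visits take place in the setting of the allocated arm.

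**The concern.** A per-protocol analysis has a recognised place in a non-inferiority trial, because departures from the allocated programme tend to pull the arms together. Here it stands alone, and its stated rule concerns completion of follow-up rather than adherence to the programme. As written it is a complete-case analysis, so comparability of the arms depends on loss being unrelated to outcome within each arm.

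That is hard to take for granted. Patients know their arm, and the arms differ in where care is given: one hospital sleep unit, or the patient's own primary care unit. Loss could differ between arms for reasons of travel, waiting or response to treatment. That it will differ is an inference, and the documents do not show in which direction.

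Two things are at stake. A biased completer difference could lead to a wrong non-inferiority conclusion or hide a right one. And the efficacy conclusion and the cost-effectiveness ratio, both main objectives under Aims, could report different ESS effects from one trial with no stated way to reconcile them.

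**Working it through.** **Inputs.** From the protocol article: 280 randomised 1:1 (140 per arm), 30% loss, margin 2 points, SD 5.9, alpha 0.05, power 0.80. Assumptions, not in the documents: the gains of completers and non-completers, and the split of loss between arms. *Gain* means improvement in ESS; differences are PC minus SU, so a negative value is worse for PC.

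**1. The plan's own figure.** With one-sided alpha 0.05 and a true difference of 0:

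n per arm = 2 × [SD × (z₀.₉₅ + z₀.₈₀) / margin]² = 2 × [5.9 × (1.645 + 0.842) / 2]² = 107.6, so 108.

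107.6 × 1.30 = 139.9, so 140 per arm and 280 in total. The stated size is reproduced with loss added as a factor of 1.30. (Dividing by 0.70 would give 153.7 per arm; that is a separate matter.)

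**2. Patients outside the test.** 0.30 × 280 = 84 excluded; 140 × 0.70 = 98 per arm remain.

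**3. Completer against all-randomised difference.** Let completers in both arms gain g and non-completers gain 0.

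- Completer difference = g − g = 0.
- All-randomised difference = (1 − loss in PC) × g − (1 − loss in SU) × g = (loss in SU − loss in PC) × g.

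| Loss PC / SU | g = 2 | g = 3 | g = 4 |
|---|---|---|---|
| 40% / 20% | −0.4 | −0.6 | −0.8 |
| 35% / 25% | −0.2 | −0.3 | −0.4 |
| 30% / 30% | 0 | 0 | 0 |
| 25% / 35% | +0.2 | +0.3 | +0.4 |
| 20% / 40% | +0.4 | +0.6 | +0.8 |

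For g = 3 at 40%/20%: 0.60 × 3 − 0.80 × 3 = 1.8 − 2.4 = −0.6. With the losses reversed it is +0.6. The completer analysis shows 0 in every cell. Every row keeps overall loss at 30%.

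**4. What a 0.6-point bias does to the test.** Take 98 per arm and one-sided 0.05. The standard error is 5.9 × √(2/98) = 0.843, and 0.6 / 0.843 = 0.712.

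- *Completer estimate too favourable to PC by 0.6, true all-randomised difference at −2:* chance of declaring non-inferiority = 1 − Φ(1.645 − 0.712) = 17.5%, against a nominal 5%.
- *Completer estimate too unfavourable by 0.6, same truth:* 1 − Φ(1.645 + 0.712) = 0.9%. The false-claim risk falls, but so does power when the true difference is 0: Φ((2 − 0.6) / 0.843 − 1.645) = 50.6%, against Φ(2 / 0.843 − 1.645) = 76.7% without bias.

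Both directions do harm: one to the validity of a positive claim, the other to the chance of making a correct one.

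**5. Data available for imputation.** ESS at 15 days, 1 and 3 months is stated only for CPAP patients. A patient without OSA who misses the 6-month visit has baseline ESS and nothing after it. A repeated-measures model alone would therefore add little outside the CPAP group.

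**The case against.** The strongest reply is that the article is a condensed document, that its verb (*will include*) does not exclude further analyses, and that per-protocol analysis is accepted practice in non-inferiority trials. Imputation methods and detailed set definitions commonly sit in an analysis plan that is not shown. All of this is fair and softens the point. It does not remove it: the article states the exclusion rule, and the completer set is the only one it ties to the −2 margin.

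Three stronger readings are tempting, and the documents do not support them.

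- *The completer analysis favours a false non-inferiority result.* The direction is unknown. If travel and referral caused more loss in the SU arm, the model above makes the completer analysis conservative for PC. Equal loss gives no bias in that model.
- *The set keeps patients who were managed in the other setting.* The article does not say how they are handled. Only one exclusion is stated, but visits are to be held in the allocated setting, so completing follow-up could be read as completing it there.
- *Intention-to-treat is reserved for costs.* The cost-effectiveness analysis covers ESS and EuroQol-5D as well. An all-randomised ESS difference is thus implied, though not one tested against the margin. Using different sets for an efficacy and an economic question is not in itself an error.

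**Conclusion.** The point holds in a limited form. The ESS non-inferiority claim is tied to a completer set from which 84 of 280 patients are expected to be missing, in an open-label trial, with no all-randomised comparison against the margin named beside it. The same outcome is taken by intention-to-treat for cost-effectiveness.

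The possible bias has no fixed sign. Under the assumptions shown (gain of 2 to 4 points in completers, none in non-completers, a 20-point gap in loss between arms) it is 0.4 to 0.8 points, or 20% to 40% of the margin. It halves for a 10-point gap and vanishes with equal loss. These are illustrations; the 30% is a planning figure, and neither the split of loss nor the outcomes of those lost can be derived from the documents. That uncertainty is why the completer analysis should not stand alone.

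**What to change.** 1. Add an ESS analysis of covariance of all randomised patients in the allocated arm, tested against the −2 margin. Claim non-inferiority only if it and the per-protocol analysis agree.
2. Impute missing 6-month ESS by multiple imputation from baseline variables, adding interim ESS where it exists (chiefly CPAP patients). Add a delta (tipping-point) sensitivity analysis, with the shift varied separately by arm. This matters most for patients without OSA, who have no interim visit.
3. Define the per-protocol set by management in the allocated setting as well as by completion of follow-up, and state how patients managed in the other setting are treated.
4. Use the same all-randomised ESS effect in the cost-effectiveness analysis.

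The cost is wording and some extra programming, with no new patients or visits. The downside is that the claim becomes slightly harder to make, because two sets must agree. For patients with no ESS after baseline, the result will lean on the imputation assumptions, which the tipping-point analysis should make visible.

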### Randomization and intervention

Randomization will be performed using an automated password-protected system, stratified by center. Each enrolled patient will be allocated in a 1:1 ratio to either the SU or PC arm. A total of 280 patients will be randomized (140:140). The patients randomized to the SU arm will be forwarded to the SU of Hospital Arnau de Vilanova—Santa Maria. In the SU, the patients will be diagnosed using PSG or RP as per usual clinical practice. Excessive daytime sleepiness will be measured using the validated Spanish version of the ESS.^20^ Patient follow-up and monitoring will be performed by SU personnel. In the PC arm, PC physicians will administer the ESS and request sleep testing from an external enterprise that supplies home respiratory therapies in the study area (the personnel of this enterprise have adequate training and expertise). Sleep tests will be performed using RP devices that meet the requirements for producing level III evidence proposed by the American Sleep Disorders Association. A full report will then be forwarded to the PC physician, who will choose an appropriate therapeutic option and perform monitoring and follow-up. The PC physicians will receive training from SU personnel before the study starts.

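### The ESS covariance model should name baseline and centre, and the non-inferiority limit needs a sensitivity analysis for clustering among the 11 primary care units

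*Protocol article*

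**What the plan says.** On allocation, the section Randomization and intervention states: "Randomization will be performed using an automated password-protected system, stratified by center". Individual patients are allocated 1:1, 140 to each arm. The section Subjects lists 11 PC units, and SU-arm patients all go to one hospital sleep unit. In the PC arm the PC physician chooses the treatment and does the monitoring, although an external company performs the sleep tests. The section Follow-up adds: "All follow-up visits will be held at the PC unit or SU according to the patient’s study arm".

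On analysis, the section Statistical analysis says of the primary outcome: "Adjusted analysis of covariance will be used to compare changes in ESS before and after the intervention in each study arm", with "non-inferiority margin = −2 points". The word for adjustment is there but the covariates are not. For EuroQol-5D and adherence the same section names chi-square tests and t-tests, or non-parametric equivalents. The section Study variables and data collection has both ESS and EuroQol-5D recorded at recruitment and at 6 months.

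The section Sample size calculation gives "an alpha error = 0.05, a beta error = 0.2, a non-inferiority limit of −2", "a common standard deviation for the two groups of ±5.9 for the principal variable" and "A loss of 30% will be assumed". It gives no intra-centre correlation and no design effect.

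**The concern.** Two features of the design bear on the width of the confidence interval, and they act in opposite directions.

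- **Centre as stratum.** Randomisation balances the arms within each centre. A model without centre leaves between-centre variation in the residual, so the interval is a little too wide.
- **Centre as provider of care.** After randomisation, PC patients of one unit share physicians and local practice. SU patients do not share a unit-level effect that varies across centres, because there is one SU. This is a partially nested design: PC outcomes may be correlated within unit. An ordinary covariance model has a single residual term and takes patients as independent.

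The second feature matters more, because the primary decision compares one confidence limit with the margin of 2 ESS points. An understated standard error favours declaring PC management non-inferior. EuroQol-5D feeds the cost-effectiveness objective, and there the stated tests, in standard form, make no use of centre and do not adjust for baseline. A t-test of changes would subtract the baseline but not adjust for it.

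**Working it through.** **Inputs.** From the protocol article: alpha 0.05 (sidedness not stated), beta 0.2, margin 2, SD 5.9, loss 30%, 140 per arm, 11 PC units, one SU. Assumed, because the document gives none: intra-centre correlation ρ of 0.01 to 0.10.

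**Step 1: the plan's own figure.** With one-sided alpha 0.05, a true difference of zero and independent patients, n per arm = 2 × 5.9² × (1.645 + 0.842)² / 2² ≈ 107.6, so 108. Then 108 × 1.3 = 140.4, which matches 140 per arm and 280 in total. One-sided 0.025 gives 137 per arm before loss and does not match. No clustering term is needed to reach 280, so the size rests on independence.

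**Step 2: standard error under independence.** Completers: 140 × 0.7 = 98 per arm, or 98/11 = 8.9 per PC unit (m). SE = 5.9 × √(2/98) = 0.843. The half-width of the 90% interval is 1.645 × 0.843 = 1.39. Power = Φ(2/0.843 − 1.645) = 0.77.

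**Step 3: two scenarios for the true SE.**

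- A, a centre effect shared by both arms, with centre left out of the model: true SE / model SE = √(1 − ρ).
- B, clustering in the PC arm only: design effect DE = 1 + (m − 1)ρ in that arm, and true SE / model SE = √((DE + 1)/2).

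In both, one-sided error = 1 − Φ(1.645 / ratio). The ratio and the error do not depend on the SD of 5.9. Power in B with the right SE is Φ(2 / (0.843 × ratio) − 1.645).

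| ρ | A: ratio | A: error | B: DE | B: ratio | B: error | B: power |
|---|---|---|---|---|---|---|
| 0.01 | 0.995 | 0.049 | 1.08 | 1.02 | 0.053 | 0.75 |
| 0.02 | 0.990 | 0.048 | 1.16 | 1.04 | 0.057 | 0.74 |
| 0.05 | 0.975 | 0.046 | 1.39 | 1.09 | 0.066 | 0.70 |
| 0.10 | 0.949 | 0.042 | 1.79 | 1.18 | 0.082 | 0.64 |

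With no loss (140 per arm, m = 12.7) the ratios in B are 1.03, 1.06, 1.14 and 1.26.

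**Step 4: does adding centre as a fixed effect help?** This was simulated with 98 per arm spread evenly over 11 centres, a true difference at the margin, no baseline covariate and 8,000 trials per setting. The Monte Carlo standard error is about 0.002 to 0.003.

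| Shared ρ | PC-arm ρ | Error without centre | Error with centre fixed effect |
|---|---|---|---|
| 0 | 0 | 0.052 | 0.052 |
| 0.05 | 0 | 0.048 | 0.053 |
| 0 | 0.05 | 0.071 | 0.072 |
| 0.05 | 0.05 | 0.062 | 0.068 |

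A centre fixed effect brings the standard error into line with the stratified design but leaves the PC-arm clustering untouched. The last row nets the two: at equal correlations of 0.05 the inflation prevails.

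**The case against.** A reader might infer that the plan ignores centre and that its non-inferiority limit therefore has the wrong width. The text does not support this. The covariance model is called adjusted and its covariates are not listed, so centre may be among them. A condensed article commonly leaves the covariate list to the full protocol or analysis plan, which is not shown. Even if centre were omitted, the error would be conservative. This part of the objection stands.

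A reader might also treat this as the error of analysing a cluster-randomised trial at patient level. It is not. Patients are randomised individually within centre, so an effect common to both arms largely cancels. Only a PC-specific care effect that differs between units can inflate the error, and the document offers no estimate of it.

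Several features also limit such an effect. One external company does the sleep tests in the PC arm, SU staff train the PC physicians, and the CPAP prescribing guideline, the titration device and the follow-up schedule are common to both arms. That argues for the lower part of the assumed range, where the error is 5.3% to 5.7%. It does not remove the possibility, because treatment choice and monitoring stay with each PC unit.

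Finally, whether PC units should be random or fixed depends on whether the inference is to PC units in general or to these 11. The Discussion's hope of a new model of care points to the former but does not settle it. For that reason, and because a random unit effect with few degrees of freedom costs power, the nested model is better placed as a sensitivity analysis than as the primary model.

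**Conclusion.** The point holds as a modest, cheap improvement and not as a demonstrated error. Neither an ordinary covariance model nor the t-tests stated for EuroQol-5D have a term for PC-unit care effects, and adding centre as a fixed effect would not supply one. If such effects exist, the non-inferiority interval is too narrow. For an assumed PC-arm correlation of 0.01 to 0.05 and 98 completers per arm, the true standard error is 2% to 9% larger than the model's and the one-sided error is 5.3% to 6.6%. At 0.10 it is 8.2%.

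These sizes rest on the assumed correlation, on equal numbers per unit and on a one-sided alpha of 0.05. If there is no PC-unit effect there is no inflation.

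The power figures in scenario B should be set against 77%, not the planned 80%. The drop from 80% to 77% comes from how the 30% loss was added, which is a separate matter. At a correlation of 0.01 to 0.02 clustering itself costs about 1 to 3 points.

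**What to change.** 1. Name baseline ESS and centre (the randomisation stratum) as covariates in the primary ESS model.
2. Analyse EuroQol-5D with baseline EuroQol-5D and centre in the model, in place of the unadjusted test.
3. Prespecify, as a sensitivity analysis of the non-inferiority limit, a partially nested mixed model with a random centre effect on the PC side only and a small-sample correction of the degrees of freedom. Report the estimated intra-centre correlation with it.

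Centre is already recorded for randomisation and both baselines are already collected, so no new data are needed. The cost is 10 degrees of freedom for 11 centres in the primary model and a somewhat wider interval in the sensitivity analysis, where a small number of PC units carries the information on between-unit variation.

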## Discussion

We believe that satisfactory management of the diagnosis and treatment of patients with suspected OSA can be obtained in the PC setting by performing actions at various levels, including the interactive training of PC teams, the sharing of electronic medical records between PC units and SUs, and the use of current technology. We expect that the included patients will achieve a comparable level of clinical response, satisfaction, treatment compliance, and complication avoidance in both the PC and SU settings. In addition, we expect that PC management will be more cost-effective than the standard SU management. Overall, we believe that this project could establish a new paradigm for the management of a common condition that involves different levels of care as well as new technologies, and could demonstrate the ability to cost-effectively manage this chronic disease in the PC setting.
